# Multicentre individual randomised controlled trial of screening and brief alcohol intervention to prevent risky drinking in young people aged 14–15 in a high school setting (SIPS JR-HIGH): study protocol

**DOI:** 10.1136/bmjopen-2016-012474

**Published:** 2016-12-23

**Keywords:** Alcohol, Brief Intervention, Randomised Controlled Trial, School Setting

## Abstract

**Introduction:**

Drinking has adverse impacts on health, well-being, education and social outcomes for adolescents. Adolescents in England are among the heaviest drinkers in Europe. Recently, the proportion of adolescents who drink alcohol has fallen, although consumption among those who do drink has actually increased. This trial seeks to investigate how effective and efficient an alcohol brief intervention is with 11–15 years olds to encourage lower alcohol consumption.

**Methods and analysis:**

This is an individually randomised two-armed trial incorporating a control arm of usual school-based practice and a leaflet on a healthy lifestyle (excl. alcohol), and an intervention arm that combines usual practice with a 30 min brief intervention delivered by school learning mentors and a leaflet on alcohol. At least 30 schools will be recruited from four regions in England (North East, North West, London, Kent and Medway) to follow-up 235 per arm. The primary outcome is total alcohol consumed in the last 28 days, using the 28 day Timeline Follow Back questionnaire measured at the 12-month follow-up. The analysis of the intervention will consider effectiveness and cost-effectiveness. A qualitative study will explore, via 1:1 in-depth interviews with (n=80) parents, young people and school staff, intervention experience, intervention fidelity and acceptability issues, using thematic narrative synthesis to report qualitative data.

**Ethics and dissemination:**

Ethical approval was granted by Teesside University. Dissemination plans include academic publications, conference presentations, disseminating to local and national education departments and the wider public health community, including via Fuse, and engaging with school staff and young people to comment on whether and how the project can be improved.

**Trial registration trial:**

ISRCTN45691494; Pre-results.

Strengths and limitations of this studyA robust randomised controlled study design.Validated screening tools used to measure attitudes and behaviours.Limited prior research has explored the use of alcohol brief interventions in UK school settings.This definitive trial follows on from a successful pilot feasibility trial.The study relies on recruitment of sufficient school sites and willingness of learning mentors to engage with the trial.

## Background

Adolescents in England are among the heaviest drinkers in Europe.^1^ The percentage of young people who have ever had an alcoholic drink in England increases with age from 10% of adolescents aged 11–12 years to 34% of adolescents aged 13–15 years, and the prevalence of drinking in the last week rises from 1% of 11year olds to 18% of 15year olds making them an important age group to target.^2^ In recent years, the proportion of adolescents who drink alcohol has fallen, although consumption among those who do drink has actually increased.^2^ Alcohol can have adverse impacts on health, well-being, education and social (including learning) outcomes for many young people who are drinking alcohol. The impact of alcohol on the development and behaviour of young people has been well researched in early,^3^ middle^4^ and late adolescence.^5^ It is now well known that young people are much more vulnerable than adults to the adverse effects of alcohol, due to a range of physical and psycho-social factors which often interact.^6^

There is no standardised definition of risky drinking in young people and so our definition encompasses commonly understood concepts of hazardous drinking (at a level or pattern that increases the risk of physical or psychological problems), harmful drinking (defined by the presence of these problems) and binge drinking (risky single occasion, high-intensity drinking which can be episodic) as well as the Department of Health concepts of increasing and high-risk drinking.^7^ The Chief Medical Officer for England has provided recommendations on alcohol consumption in young people^8^ based on an evidence review of the risks and harms of alcohol to young people.^6^ The recommendations state that children should abstain from alcohol before the age of 15 and those aged 15–17 are advised not to drink, but if they do drink it should be no more than what equates to adult daily benchmarks.^9^

### Primary and secondary preventative interventions for risky drinking

There is a large volume of research on universal prevention to reduce risky drinking in the school setting.^10^
^11^ Such prevention is directed at all young people, whether they drink alcohol or not, and aims to delay the age that drinking begins, often via general health education. This body of work has shown mixed results with only a small number of programmes reporting that interventions delivered in a school setting were more effective in reducing alcohol use than control conditions.^12^ Secondary prevention, that is, targeting interventions at young people who are already drinking alcohol, may be a more effective and efficient strategy since the intervention is likely to have more salience for the individuals receiving it.^13^
^14^

This secondary prevention generally consists of alcohol brief interventions and screening (to identify relevant potential recipients) followed by structured advice or counselling of short duration which is aimed at reducing alcohol consumption or decreasing problems associated with drinking.^15^ The interventions are often based on social cognitive theory which is derived from social learning theory.^16^ These types of intervention have been found to be particularly effective with this age group.^13^

This current research aims to develop the evidence base by focusing on a secondary prevention intervention of screening and brief intervention to reduce risky drinking in younger adolescents (aged 14–15) in a school context. The study follows on from the SIPS JR-HIGH pilot feasibility study which was funded by the National Institute of Health Research Public Health Programme (NIHR PHR) (ISRCTN07073105).^14^

## Main trial

### Aims, objectives and methods

#### Research aim

The aim of the study is to evaluate the effectiveness and cost-effectiveness^i^ of alcohol screening and brief intervention to reduce risky drinking in young people aged 14–15 in the English school setting. Validated tools will be used in the study for primary and secondary outcomes measures.

#### Primary outcome

The primary outcome of the trial is total alcohol consumed in standard units in the last 28 days, using the 28 day Timeline Follow Back questionnaire^17^ at 12-month follow-up.

#### Baseline secondary outcome measurements

Student Alcohol Questionnaire (A-SAQ)^18^ to measure risky drinking (scoring ‘4 or more times but not every month’, ‘at least once a month but not every week’, ‘every week but not every day’, or ‘every day’);Alcohol use frequency, quantity (on a typical occasion) and binge drinking (six or more drinks in one session for men and women)^19^ assessed using the modified 10 question Alcohol Use Disorders Identification Test (AUDIT);^20^
^21^Alcohol-related problems assessed using the validated Rutgers Alcohol Problems Inventory (RAPI) which includes measures on aggression;^22^Drunkenness during the last 30 days, dichotomised as ‘never’ and ‘once or more’;^4^Drinking motives assessed using the 20-item Drinking Motives Questionnaire (DMQ). This tool uses a six-point Likert scale, which measures motives to drinking across four domains (social, coping, enhancement and conformity). Higher scores within each domain indicate stronger endorsement of positive reinforcement received through consumption of alcohol;^5^General psychological health using the 14-item Warwick Edinburgh Mental Well-Being Scale (WEMWBS).^23^ This tool uses a 5-point Likert scale which gives a score of one to five per question giving a minimum score of 14 and maximum score of 70. A higher WEMWBS score indicates a higher level of mental well-being;^24^
^25^Two questions relating to sexual risk taking are included. These are the same questions as in the pilot study.^14^ These questions are: ‘After drinking alcohol, have you engaged in sexual intercourse that you regretted the next day?’ and ‘After drinking alcohol, have you ever engaged in sexual intercourse without a condom?’ Both questions can be answered with one of the three following options: ‘I have never engaged in sexual intercourse’, ‘Yes’, or ‘No’;Energy drink consumption will be assessed by asking young people how many times a week they consume energy drinks. Young people can answer: ‘never’, ‘less than once a week’, ‘2–4 days a week’, ‘5–6 days a week’, ‘every day once a day’ and ‘every day more than once a day’;Age of first smoking and how many cigarettes were smoked in the past 30 days;^1^Demographic information collected will include gender and ethnicity. The first part of the postcode will be collected for trial participants;Quality of life measured using the EQ-5D Y, which is a valid measure for those aged 12 or older, and will be used to measure health-related quality of life.^26^ Responses to the five items will be converted into utility scores using the UK population algorithm. This will be administered at baseline and 12 months post intervention;^26^Quality-adjusted life years (QALY) estimated using general population tariffs from responses to EQ-5D Y administered and scored at baseline and 12 months.

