#### 12-Month follow-up measurements

All tools assessed at baseline;Per cent days abstinence over last 28 days, drinks per drinking day and days>2 units from 28 day TLFB;Incremental cost per QALY gained at 12 months;Depending on findings, modelled estimates of incremental cost per QALY and cost-consequences in the longer term;National Health Service (NHS), educational, social and criminal services data estimated using a modified S-SUQ^27^ and a learning mentor case diary developed in the pilot study, measured at 12 months post intervention;Cost-consequences presented in the form of a balance sheet for outcomes at 12 months. (For further details, see online supplementary appendix 1).

10.1136/bmjopen-2016-012474.supp1supplementary appendix

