#### 12-Month follow-up

Follow-up will occur 12 months post intervention. All young people who are randomised into the trial will be invited to meet with the Research Coordinator (in school) where they will be asked to complete the same questionnaires used at baseline. The researcher will be blinded to the condition the young person was allocated to. The TLFB (including the primary outcome measure of total alcohol consumption) will also be completed face-to-face in schools with the researcher in order to limit bias in the results. All trial participants will be given an admit-one cinema voucher, to compensate them for their time involved in the study.^30^ Trial participants' baseline and follow-up questionnaires will be linked with a unique ID (the screening number). All participants will be asked by the researcher at follow-up whether they are willing to be contacted for an in-depth interview by a researcher who may be the same individual or another researcher.

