#### Primary outcome

The primary effectiveness analysis will be by intention-to-treat. Multiple linear regression will be used to compare the primary outcomes between the two randomisation groups at 12 months, adjusting for any imbalance in key covariates, including school.

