#### Secondary outcomes

The secondary outcomes will be analysed in a similar manner. Comparisons of means will be presented as mean differences or ratios of geometric means (if a logarithmic transform is necessary for skewed data) with 95% CIs  ORs and 95% CIs will be presented for binary outcomes. Exploratory analyses will also be undertaken, for example, to examine differences in outcome by gender, deprivation and extent of intervention received, though there is limited power to investigate these comparisons. These moderators have been included so as to consider whether the ABI may need to be targeted when delivered, should it be shown to be effective. We will consider any difference in attrition rates, and any non-randomness of the attrition, when comparing outcomes between the two groups. The pattern of missing observations because of loss to follow-up will be examined to determine the extent of missingness, and whether it is missing at random or is informative. If data are missing to a sufficient extent, the use of appropriate multiple imputation techniques will be considered.

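### The two sexual-risk items have no post-baseline window and are repeated unchanged at 12 months, so they cannot show later behaviour in pupils already 'Yes' at baseline

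*Protocol article*

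**What the plan says.** All references are to the Protocol article.

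- Baseline secondary outcome measurements prints both items. The condom item reads "After drinking alcohol, have you ever engaged in sexual intercourse without a condom". The regret item reads "After drinking alcohol, have you engaged in sexual intercourse that you regretted the next day". The first asks about the whole lifetime; the second contains neither 'ever' nor a period.
- The same section gives the answers: "Both questions can be answered with one of the three following options: ‘I have never engaged in sexual intercourse’, ‘Yes’, or ‘No".
- 12-Month follow-up measurements begins its list with "All tools assessed at baseline". The 12-Month follow-up section under Data collection says of the pupils that "they will be asked to complete the same questionnaires used at baseline".
- Analysis, Secondary outcomes, says "The secondary outcomes will be analysed in a similar manner" and that "ORs and 95% CIs will be presented for binary outcomes". The primary analysis to which this refers is a regression "adjusting for any imbalance in key covariates, including school".

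The article gives no follow-up version of the items with a post-baseline window, no restriction to pupils who were not 'Yes' at baseline, and no mention of the baseline answer as a covariate.

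**The concern.** An outcome compared between arms at 12 months should be able to change after randomisation. A truthful 'Yes' to a lifetime question cannot. For pupils who give it at baseline, the follow-up answer is settled before allocation and is the same in both arms. In the other pupils a follow-up 'Yes' is a new event. Reading the follow-up answer alone mixes the two.

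Two things are at stake. First, the trial cannot learn whether pupils already exposed changed their behaviour, since neither item asks about it. Second, if the arms are compared without regard to the baseline answer, a real difference in new events looks smaller than it is. The article uses recall windows elsewhere: 30 days for drunkenness and cigarettes, 28 days for the Timeline Follow Back and 12 months for the screening question.

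**Working it through.** **Inputs from the article.** 235 pupils followed up per arm, 1:1 allocation and a 5% significance level (taken as two-sided). No figure is given for the sexual-risk items.

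**Check of the stated sample size.** For a standardised difference of 0.3 and 90% power, n per arm = 2 × (1.960 + 1.282)² / 0.3² = 233.5, rounded up to 234. At 235 per arm the power is 90.2%. The stated 235 reproduces. It serves below only as the number of pupils per arm.

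**Model.** Let b be the share already 'Yes' at baseline, the same in both arms by randomisation. Let q0 (control) and q1 (intervention) be the risks of a first event over follow-up among the rest. With truthful answers, the proportion 'Yes' at 12 months is

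p = b + (1 − b)q, and 1 − p = (1 − b)(1 − q).

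The OR that ignores the baseline answer is

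OR = {[b + (1 − b)q1] / (1 − q1)} ÷ {[b + (1 − b)q0] / (1 − q0)}.

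With b = 0 this is the OR for new events. For any b above 0 it lies nearer 1 whenever q1 and q0 differ. The direction follows from algebra; the size depends on b, q0 and q1, all of which are assumptions here.

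**Small effect.** Assume q0 = 10% and q1 = 7%. The new-event OR is (0.07/0.93) / (0.10/0.90) = 0.68. For b = 20%:

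- control: 0.20 + 0.80 × 0.10 = 0.280
- intervention: 0.20 + 0.80 × 0.07 = 0.256
- OR = (0.256/0.744) / (0.280/0.720) = 0.88

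| b | Control 'Yes' | Intervention 'Yes' | OR ignoring baseline |
|---|---|---|---|
| 2% | 11.8% | 8.9% | 0.73 |
| 5% | 14.5% | 11.7% | 0.78 |
| 10% | 19.0% | 16.3% | 0.83 |
| 20% | 28.0% | 25.6% | 0.88 |
| 30% | 37.0% | 34.9% | 0.91 |

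At b = 20%, power with 235 per arm is about 9% on the lifetime answer. It is about 18% when only new events are counted among the 0.80 × 235 = 188 pupils per arm still at risk.

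**Larger effect.** Assume q0 = 20% and q1 = 10%, a new-event OR of 0.44.

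| b | OR ignoring baseline | Power, lifetime answer | Power, new events only |
|---|---|---|---|
| 5% | 0.54 | 74% | 84% |
| 10% | 0.60 | 63% | 82% |
| 20% | 0.69 | 46% | 78% |
| 30% | 0.75 | 34% | 72% |

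**A 12-month window at follow-up.** Assume b = 20%, a true OR of 0.5 in every pupil, and a 12-month control risk of 50% in baseline-'Yes' pupils and 15% in the others. A question about the last 12 months gives 22.0% against 13.2%, OR 0.54 and power 71%. The lifetime question gives 32.0% against 26.5%, OR 0.77 and power 26%. The windowed item gains because it also measures the pupils already exposed.

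**The case against.** The strongest reply is that the article does not say how these items are analysed. They have three response options, no dichotomy is stated (as it is for drunkenness), and the sentence on ORs does not name them. Baseline and follow-up questionnaires are linked by a unique ID, so the baseline answer is available. Conditioning on it, or counting only new events, would remove the dilution under the model above, and an analysis plan that is not shown may do so. This stands: a reader might infer that the reported OR will be diluted, but the documents support that only for an OR that ignores the baseline answer. It does not remove the whole point. The wording and its reuse are fixed in the article, and no analysis can recover later behaviour in baseline-'Yes' pupils from a question that does not ask about it.

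Three further limits also stand.

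- A reader might call both items lifetime questions. Only the condom item says so; the regret item is open-ended because no period is printed, and the form itself is not shown.
- A reader might infer that a null result would be an artefact of the wording. Under the small-effect assumption power is low either way (about 18% against 9% at b = 20%), so sample size alone could produce a null result.
- No passage supports the idea that pupils already 'Yes' are especially common in this sample. If few are, the distortion is small.

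That the items come from the pilot explains their wording but does not give them a window.

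**Conclusion.** The point holds as a minor one, confined to two secondary items. A truthful baseline 'Yes' to the condom item, and to the regret item if read as open-ended, is bound to recur at 12 months. The repeated item therefore cannot show change in those pupils, and an OR that does not condition on the baseline answer moves toward 1.

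The size is not known from the documents. Under assumed new-event risks of 10% and 7%, an OR of 0.68 becomes 0.73 to 0.91 as the baseline 'Yes' share goes from 2% to 30%. Under 20% and 10%, an OR of 0.44 becomes 0.54 to 0.75 for shares of 5% to 30%. These figures assume truthful answers and an equal baseline share in both arms. A null result on these items could partly reflect their wording; nothing stronger is supported. The primary outcome, the sample size and the main conclusion are untouched.

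**What to change.** At the 12-month visit, ask both items about the period since baseline or the last 12 months. Follow-up takes place 12 months after the intervention, so a 12-month window fits the time at risk. The cost is a change to two questions on the follow-up form, notified to the ethics committee, and a small loss of identity with the baseline wording.

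If the form can no longer be changed, define the outcome as a new 'Yes' at 12 months among pupils who were not 'Yes' at baseline. Count the option for pupils who have never had intercourse as no event, at both time points. The cost is a somewhat smaller analysis set (188 rather than 235 per arm if 20% were already 'Yes'). This version removes the dilution but still leaves later behaviour in baseline-'Yes' pupils unmeasured, and the report should say so.

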#### 12-Month follow-up measurements

All tools assessed at baseline;Per cent days abstinence over last 28 days, drinks per drinking day and days>2 units from 28 day TLFB;Incremental cost per QALY gained at 12 months;Depending on findings, modelled estimates of incremental cost per QALY and cost-consequences in the longer term;National Health Service (NHS), educational, social and criminal services data estimated using a modified S-SUQ^27^ and a learning mentor case diary developed in the pilot study, measured at 12 months post intervention;Cost-consequences presented in the form of a balance sheet for outcomes at 12 months. (For further details, see online supplementary appendix 1).

10.1136/bmjopen-2016-012474.supp1supplementary appendix

### Trial participants

Young people aged 14–15 years in Year 10 in at least 30 Secondary/High schools/Academies in four areas: the North East of England, North West of England, Kent and Medway, and London. Schools will be included if they have learning mentors (or equivalent members of pastoral staff, including teachers fulfilling this role) employed by the school (most schools have these pastoral/learning mentor staff roles). Screening will take place in the personal, social and health education (PSHE) or equivalent lesson, registration class, on a classroom basis, or in assembly. Interventions will take place in the learning mentor's classroom or office space. Pupils receive minimal recompense for taking part in the trial (an ‘admit one’ cinema voucher), and each participating school will receive £1000 to assist with administration and other costs of full research participation.

#### Inclusion criteria

Young people aged 14–15 years inclusive, whose parents do not opt them out of the study, scoring positively on the A-SAQ, leaving their name, and are willing and able to provide informed written assent (see online supplementary appendix 2) for intervention and follow-up.

10.1136/bmjopen-2016-012474.supp2supplementary appendix

#### Exclusion criteria

Young people already seeking or receiving help for an alcohol use disorder, with a recognised diagnosis of a mental health disorder, or exhibit challenging behaviour.

### Trial procedures

Learning mentors (or equivalent members of pastoral/trained staff; hereafter referred to as ‘learning mentors’) employed by schools will deliver the intervention. All learning mentors will receive school-based training in the study procedures and intervention. Training for learning mentors will be carried out by the trained Research Coordinators. Simulated scenarios between learning mentors will be audio-recorded and learning mentors will be assessed by an interventionist prior to embarking on the study with more training support offered if needed. Learning mentors will be provided with materials and on-going guidance and supervision will be provided by research staff. Support on implementing screening and paperwork relevant to the research will be provided by the research team, with a Research Coordinator in each geographical site. Research staff and trainers will maintain regular contact with schools throughout the study period, including site visits and telephone and email support.

